### Data management and monitoring

Acquired data will be entered immediately into an Electronic Data Capture System at each center. Data review and verification will be conducted by a person who did not perform the initial entry. Onsite monitoring will be conducted periodically by dedicated staff of the Data Management division at NCNP (these staff members are independent from this study). The Data and Safety Monitoring Board will oversee the trial data and ethics, with an independent chair and two independent members. The members of the committee are independent from the sponsor and competing interests of the present study. The principle investigator (TA) will submit an annual progress report to the Data and Safety Monitoring Board.

### Safety

Information on serious adverse events (SAEs) will be collected from the TAU medical doctor or CBT-IE therapist during the intervention. Based on the Ethics Guideline for Clinical Research (Ministry of Health, Labour and Welfare (MHLW)), an SAE is defined as ‘an adverse event that may lead to death or to enduring severe impairment depending on the patient’s conditions and circumstances’ and will include any one of the following outcomes:Results in death (all deaths regardless of causal relationship with the intervention or for which a causal relationship with the intervention cannot be excluded, during the intervention phase or up to 30 days after the completion of the intervention)Is life threatening, or places the participant at immediate risk of death from the event as it occurredRequires or prolongs hospitalizationCauses persistent or significant disability or incapacityResults in congenital anomalies or birth defectsIs another condition which investigators judge to represent significant hazards

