**Methods:**

This study will be a multicenter, parallel-design RCT. Participants diagnosed with IBS according to the Rome IV diagnostic criteria will be randomized to either the treatment as usual (TAU) group or the CBT-IE-w/vid + TAU group. CBT-IE-w/vid consists of 10 sessions (approximately 30 min face-to-face therapy + viewing a video prior to each session). Patients in the CBT-IE-w/vid group will be instructed to pre- view 3- to 13-min videos at home prior to each face-to-face therapy visit at a hospital. The primary outcome is the severity of IBS symptoms. All participants will be assessed at baseline, mid-treatment, post-treatment, and follow-up (3 months after post assessment). The sample will include 60 participants in each group.

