### Planned interventions

#### CBT - interoceptive exposure with complementary video materials (CBT-IE-w/vid)

Participants receive CBT using interoceptive exposure for IBS with complementary psychoeducational video materials (CBT-IE-w/vid**)**. The original IE program [15] consists of 10 weekly sessions of approximately 60 min. Our CBT-IE-w/vid intervention consists of 10 weekly sessions, but the time length of each session has been changed. Each session consists of 2 parts: viewing 3- to 13-min videos at home in advance followed by about 30-min of face-to-face therapy session with a therapist at hospital. All CBT-IE-w/vid therapists will be medical doctors who specialize in psychosomatic medicine or psychologists qualified in least one of the following: licensed by the Japanese government, clinical psychologists qualified by the Foundation of the Japanese Certification Board for Clinical Psychologists, or medical psychologists qualified by the Japanese Society of Psychosomatic Medicine.

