#### Treatment as usual (TAU)

Patients in both treatment arms will receive TAU by medical doctors. TAU is defined as standard treatment for IBS as recommended by the clinical practice guidelines of the Japanese Society of Gastroenterology [14]. According to the guidelines, a three-step strategy is adopted. The first step consists of lifestyle modification and gut-targeted pharmacotherapy for approximately 4 weeks. Non-responders to the first step intervention proceed to the second step, which includes psychopharmacological agents and brief psychotherapy in addition to the first step interventions for approximately 4 weeks. In the third step, for patients who have not obtained sufficient improvement by the second step, specific psychotherapies including CBT are recommended.

In this study, TAU will consist of only the first and second step interventions. Time spent in each TAU session is 15–30 min. The frequency of TAU sessions is usually once every 4 weeks, but it may vary depending on the patient’s schedule. There is no limit for duration of TAU in either arm. This procedure will be beneficial and ethically desirable for patients.

The medical doctor in charge will implement TAU using the common guidance reviewed by IBS experts (SF, KY, and [name]).

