### Statistical analysis

Statistical analyses will be conducted by an independent statistician (KM) who is not a TAU medical doctor or CBT-IE-w/vid therapist.Analysis set for efficacy analysis: modified intention to treat (ITT) set that includes all subjects who have at least one outcome after intervention.If possible, data from participants who drop out will be collected after dropout.Analysis for background factors: summary statistics (frequency, mean, SD) will be calculated depending on the characteristics of each variable.Primary analysis: mixed model for repeated measures (MMRM) analysis will be applied to the change from baseline for IBSSI-J at visit five (for participants in the TAU alone group the time point is defined as 6 to 10 weeks after randomization) and visit ten (for participants in the TAU alone group the time point is defined as 10 to 16 weeks after randomization), where treatment, visit, treatment-by-visit interaction, and baseline IBSSI-J are modeled as fixed effects. T-tests will then be conducted on the difference of adjusted means between the groups at visit 10.Secondary analyses: MMRM analysis will be applied to other continuous outcomes.

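### The SAE collection period stops 30 days short of the death criterion it serves, and it has no defined end for TAU alone

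*Protocol article*

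**What the plan says.** All references are to the protocol article.

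- **Safety**, collection rule: "Information on serious adverse events (SAEs) will be collected from the TAU medical doctor or CBT-IE therapist during the intervention".
- **Safety**, first SAE criterion: deaths count if they occur "during the intervention phase or up to 30 days after the completion of the intervention". No other criterion in the list carries a period after the intervention.
- **Treatment as usual (TAU)**: "Patients in both treatment arms will receive TAU by medical doctors"; "The frequency of TAU sessions is usually once every 4 weeks", with some variation; and "There is no limit for duration of TAU in either arm".
- **CBT-IE-w/vid**: "Our CBT-IE-w/vid intervention consists of 10 weekly sessions". The exclusion criteria place these sessions within a 16-week implementation period.
- **Statistical analysis**: for TAU alone, the counterpart of visit ten is given as "the time point is defined as 10 to 16 weeks after randomization". This stands in the description of the primary efficacy model. The Safety section does not refer to it.
- **Abstract, Methods**: the last assessment is the "follow-up (3 months after post assessment").

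**The concern.** Two sentences of one section set different periods. One says when SAE information is gathered; the other says which deaths are SAEs, and it reaches 30 days further. A site that follows the first sentence literally can miss deaths that the second says must count.

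Both sentences also hang on the end of the intervention. The therapy arm has a course with a last session. TAU alone has no such point, because TAU is unlimited. Sites would have to choose one, and the period over which SAEs are recorded could then differ between arms.

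Finally, therapists are named as SAE reporters and only one arm has them. The completeness of the SAE record is at stake, and so is the fairness of any table that sets SAE counts side by side by arm.

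**Working it through.** The article states no safety figure to reproduce, and its sample-size calculation does not bear on this point. The check is a comparison of the stated periods plus simple counts.

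**Inputs.** Therapy course: 10 weeks (10 weekly sessions) to 16 weeks (implementation period). Death window: course plus 30 days. TAU visits: one every 4 weeks, both arms. Therapy sessions: 10, one arm only. Follow-up: 3 months after the post assessment, taken as 13 weeks (91 days).

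**Step 1. Share of the death window outside collection**, with the intervention taken to end with the therapy course.

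Share = 30 / (course in days + 30)

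- 16-week course: 30 / (112 + 30) = 30 / 142 = 21%.
- 10-week course: 30 / (70 + 30) = 30 / 100 = 30%.

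**Step 2. What the intervention could mean.**

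| Reading | Therapy + TAU | TAU alone |
|---|---|---|
| The therapy course | Ends at session 10; the 30-day gap applies | No intervention, so no stated window |
| All assigned treatment, TAU included | No completion; collection stays open | No completion; collection stays open |
| A study period ending at visit ten or its counterpart | Ends at visit ten; the 30-day gap applies | Ends 10 to 16 weeks after randomization; the 30-day gap applies |

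The first reading leaves TAU alone without a window. The second removes the gap, but the 30-day clock never starts, so the death criterion has no meaning. The third gives comparable windows and still leaves the gap, but the article ties that time point to efficacy only. No reading makes both safety sentences work in both arms.

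**Step 3. Scheduled contacts with a named SAE reporter.**

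TAU alone = weeks / 4; therapy arm = 10 + weeks / 4

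- By week 16: 16 / 4 = 4 against 10 + 4 = 14.
- By week 10, if all sessions are done: 10 / 4 = 2.5 against 10 + 2.5 = 12.5.

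The difference is 10 contacts in each case. These are opportunities to report. They do not measure how many events are missed.

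**Step 4. Would the existing follow-up contain the 30-day rule?** Yes: 91 days exceeds 30. A window from randomization to follow-up lasts 10 + 13 = 23 to 16 + 13 = 29 weeks. One that ends 30 days (4.3 weeks) after the post-treatment time point lasts 14.3 to 20.3 weeks.

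**The case against.** The strongest case on the other side is that this is a wording slip in a condensed article. The full protocol may state the windows, and the duty to notify an SAE, under Follow-up after serious adverse event, carries no time limit. It is true that missing procedural detail would be no finding. But the two periods are both printed, and they conflict. The notification duty says what happens once an event is known. It does not say that anyone gathers information after the intervention.

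Several stronger readings are tempting, and the document does not support them:

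- **That SAEs cannot be compared between arms.** No between-arm safety analysis is stated, and both arms have a TAU doctor on the same usual 4-weekly schedule. A descriptive comparison may be biased; it is not impossible.
- **That therapy participants are observed for 10 weeks and TAU-alone participants for 16 or more.** This applies a narrow meaning of intervention to one arm and an open one to the other. TAU is unlimited in both.
- **That the whole 3-month follow-up is uncovered.** The death criterion reaches into its first 30 days, and under the open-ended reading of TAU collection need not stop at all.
- **That 14 contacts against 4 measures the bias.** The listed events are mostly deaths, hospitalizations and similar hard events, which usually remain known at the next contact. Detection need not rise in proportion to visits.

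It is also fair that a self-report question cannot capture deaths, and that positive answers need a clinician to confirm them. The fix has to allow for both.

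**Conclusion.** The point holds as a conflict within the Safety section, together with an undefined end of intervention for TAU alone. If the intervention ends with the therapy course or at the visit-ten time point, the last 21% (16-week course) to 30% (10-week course) of the death window lies outside stated collection.

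The arms' windows may differ, because the only matched time point for TAU alone belongs to the efficacy analysis. The 10 extra contacts with a named reporter make extra detection in the therapy arm the likelier direction of bias in any descriptive SAE comparison. Its size cannot be estimated from the document, and for hard events it may be small. The effect of unequal windows could go either way, depending on the end point that sites choose for TAU alone.

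The figures assume a course of 10 to 16 weeks, TAU visits at the usual interval and full session attendance. The primary efficacy analysis is not affected. The point should be corrected because the rule contradicts itself and the correction is cheap.

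**What to change.** Reconcile the two safety statements in one amended paragraph:

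1. Set one SAE collection window for both arms, counted from randomization and running at least 30 days past the post-treatment time point. The existing 3-month follow-up is a convenient common end and contains the 30-day rule.
2. For TAU alone, state the post-treatment time point for safety as well. The 10-to-16-week definition already used for efficacy would serve.
3. Put the same SAE question to every participant in both arms at the existing mid-treatment, post-treatment and follow-up assessments, and base any descriptive comparison by arm on that common schedule.
4. Keep reports by the TAU doctor or therapist open at any time within the window, including after the last session. Deaths will reach the record only by this route.

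The cost is the paragraph, one form item, and some clinician time to confirm positive answers. No visits are added and no treatment changes.

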### Follow-up after serious adverse event

When an SAE occurs, the medical doctor will take all necessary and appropriate measures to ensure the safety of the patient and will provide appropriate treatment including hospital admission. The medical doctor will immediately notify the principal investigator (TA) of the SAE, and the principal investigator will notify all collaborating investigators. The head investigator of all sites will report the SAE to the relevant authorities (Data and Safety Monitoring Board, Institutional Review Board, and President of each center) and the Japanese MHLW. The medical expenses will be borne by the patient because the treatment will be supplied as a healthcare service provided under national health insurance, the same as for usual treatment. There will be no special financial compensation; however, any negligence on the part of the physician may be covered by the doctors’ liability insurance.

### Ethical issues

The present study complies with the ethical guidelines for clinical studies published by the Japanese MHLW, as well as the ethical principles established for research on humans stipulated in the Declaration of Helsinki and further amendments thereto. This protocol has been reviewed and approved by the Institutional Review Board of the (Japanese) National Center of Neurology and Psychiatry (accepted on November 29, 2017; A2017–067) and the Ethics Committees of all four collaborating facilities.

If important protocol modifications such as changes to eligibility criteria, outcomes, or analyses are needed for any reason, the principal investigator (TA) will communicate this with the Institutional Review Boards.

Written informed consent will be obtained from all participants, who will be informed that they can withdraw from the study at any time and that their withdrawal will never lead to refusal of any other services. A medical doctor or a clinical psychotherapist in charge of the informed consent process is responsible for ensuring that informed consent is given by each patient.

Data from each participant will be handled with sequentially allocated numbers to maintain participant confidentiality. All data collected in this study will be securely stored without personal information (name, address, etc.). Access to the data is encrypted and limited to researchers affiliated with this study.

### Dissemination

The study findings will be disseminated via publications in peer-reviewed international journals. We will submit annual progress reports to the MHLW and NCNP, which are funding resources for this trial. We will also present the findings at relevant research conferences.

## Discussion

Previous studies have indicated that the standard medications (TAU), such as bulking agents and antispasmodics, have low responsiveness [40–42] and that many patients with IBS suffer from ongoing symptoms. Some meta-analyses on the efficacy of antidepressants for IBS reported that they are effective in IBS treatment [43], but several systematic reviews [44] have indicated that the efficacy of SSRI and tricyclic antidepressants did not surpass bulking agents and antispasmodics. In such circumstances, psychological treatments such as CBT have been shown to be helpful for IBS symptoms [45, 46]. However, Craske et al. [15] reported that the use of an active control leads to smaller effect sizes than studies with TAU or wait-list designs. Therefore, in this study we will assess the effectiveness of CBT-IE-w/vid in addition to TAU compared to TAU alone for improving IBS symptoms.

CBT-IE was originally developed for panic disorder and involves exercises causing physical sensations that mimic those experienced in a panic attack [16, 47]. Patients with IBS also have problems with physical sensations such as hypervigilance and hypersensitivity to sensations related to IBS symptoms [15]. Although the interoceptive exposure procedure can be a promising approach to reduce anxiety to abdominal sensation as a perpetuating factor of IBS, it has never been studied in the Japanese population. As a result, this procedure is not used clinically for IBS in Japan. In this study, we will evaluate gastrointestinal symptom-specific anxiety using VSI and body vigilance with BVS-J as possible mediators on the effect of CBT-IE on IBS symptoms. We will also assess IBS specific QOL and health related QOL as secondary outcomes. Efficacy on QOL has not been well elucidated in the previous CBT-IE study by Craske et al.

Our study has three strengths. First, it is the first RCT of CBT treatment for IBS in Japan. Second, we will utilize video materials to facilitate and shorten each face-to-face therapy session to enhance the cost-effectiveness of psychotherapy. The amount of the time necessary for a face-to-face therapy session was reduced from 66 min (face-to-face therapy alone) [21] to 38 min (using complementary video materials) [22], and the program relies more on self-administered management. Third, this is a multisite RCT (five sites in Japan), which will facilitate participant recruitment. In addition, participants recruited from five sites will provide a more reliable representation of the target patient population than a single-center study, which is favorable to implementation as well.

There are some limitations to this study. The primary endpoint in this study is a patient-reported outcome (PRO). It is desirable to set more objective outcomes as primary endpoints. However, currently there is no standard objective outcome for IBS that could be used as an objective primary endpoint. Using PRO as the primary endpoint is recommended in the guidance for clinical trials of IBS published by the United States Food and Drug Administration [48]. Moreover, bias from using PRO is expected to operate equally in both groups, rendering any observed between-group differences clinically meaningful. Also, this study is a non-blinded randomized controlled trial due to the type of intervention (psychotherapy). The impossibility of effectively blinding participants to treatment allocation in a CBT study also makes it impossible to control for placebo effects. This is a general problem in all psychotherapy studies [49].

## Abbreviations

CBT: Cognitive behavioral therapy
CBT-IE: Cognitive behavioral therapy using interoceptive exposure
CBT-IE-w/vid: CBT-IE with complimentary video materials
IBS: Irritable bowel syndrome
ITT: Intention to treat
PRO: patient-reported outcome
QOL: Quality of life
RCT: Randomized controlled trial
SAE: Serious adverse event
TAU: Treatment as usual
